## Abstract

**Background:**

Up to 50% of chronic whiplash associated disorders (WAD) patients experience considerable pain and disability and remain on sick-leave. No evidence supports the use of physiotherapy treatment of chronic WAD, although exercise is recommended. Previous randomised controlled studies did not evaluate the value of adding a behavioural therapy intervention to neck-specific exercises, nor did they compare these treatments to prescription of general physical activity. Few exercise studies focus on patients with chronic WAD, and few have looked at patients’ ability to return to work and the cost-effectiveness of treatments. Thus, there is a great need to develop successful evidence-based rehabilitation models. The study aim is to investigate whether neck-specific exercise with or without a behavioural approach (facilitated by a single caregiver per patient) improves functioning compared to prescription of general physical activity for individuals with chronic WAD.

**Methods/Design:**

The study is a prospective, randomised, controlled, multi-centre study with a 2-year follow-up that includes 216 patients with chronic WAD (> 6 months and < 3 years). The patients (aged 18 to 63) must be classified as WAD grade 2 or 3. Eligibility will be determined with a questionnaire, telephone interview and clinical examination. The participants will be randomised into one of three treatments: (A) neck-specific exercise followed by prescription of physical activity; (B) neck-specific exercise with a behavioural approach followed by prescription of physical activity; or (C) prescription of physical activity alone without neck-specific exercises. Treatments will be performed for 3 months. We will examine physical and psychological function, pain intensity, health care consumption, the ability to resume work and economic health benefits. An independent, blinded investigator will perform the measurements at baseline and 3, 6, 12 and 24 months after inclusion. The main study outcome will be improvement in neck-specific disability as measured with the Neck Disability Index. All treatments will be recorded in treatment diaries and medical records.

**Discussion:**

The study findings will help improve the treatment of patients with chronic WAD.

**Trials registration:**

ClinicalTrials.gov identifier: NCT01528579.

## Background

Whiplash associated disorders (WAD) are common [1-4], with a cumulative annual incidence as high as 600 per 100 000 inhabitants [5]. When symptoms persist for more than 6 months, WAD is considered chronic [6]. Recent studies estimate that up to 50% of WAD patients experience prolonged symptoms, including considerable pain, disability, sick leave and reduced income [7-9].

Due to the personal and societal burdens associated with chronic WAD [1,2,9], it is extremely important to determine the best possible treatment for reducing pain and restoring the ability of patients to perform everyday tasks and to return to work. A WAD diagnosis is based on a patient’s subjective description of symptoms and on clinical examination. The Quebec Task Force (QTF) classified WAD into severity grades 0–4, with grade 0 indicating no neck complaints and no physical sign(s) and grade 4 indicating a neck complaint with neck fracture or dislocation [10]. Identifying subgroups in this heterogeneous group of patients with chronic WAD could lead to a better understanding of the complexity of chronic WAD [11].

There is no consensus regarding the injury mechanism in complex WAD cases. Some symptoms of persistent WAD can be attributed to injuries involving neck structures, including joints, ligaments and muscles [12]. In particular, WAD may involve an altered activation pattern in the neck muscles [13]. Combinations of bio- and psychosocial factors, such as fear of re-injury, low mood and low self-efficacy, appear to affect recovery [14,15]. Thus, it is reasonable to assume that a combination treatment that includes both a physical and a behavioural approach might improve rehabilitative outcomes [16]. However, it is time-consuming and costly to involve several professionals in an individual’s treatment. Unfortunately, little is known about how a single caregiver can best use a combined physical and behavioural approach to treat individuals with chronic WAD [16,17]. Specifically, the effect of adding a behavioural component to neck-specific exercises is unknown. Furthermore, few studies on individuals with chronic WAD symptoms have investigated the effects of exercises that specifically target neck muscles.

Most studies of people with WAD have focused on the acute phase. The general advice given to patients in this phase of WAD is to be physically active [1,18]. There are just a few randomised controlled trials (RCTs) of the effects on exercise on chronic WAD [14,15,19-21]. Of these, two studies had small samples [15,19], and two other studies [20,21] allowed the addition of passive treatment strategies, making it difficult to determine the effects of the different treatment components. Only one larger RCT, conducted by Stewart et al. [14], included patients with WAD grade 3 and compared a 6-week exercise and behavioural programme to self-treatment based on professional advice. Pain intensity, pain bothersomeness and function were used as primary outcome measurements, and the short-term outcome favoured professional advice in combination with exercise over advice alone.

In all of the WAD RCTs to date, the effects of treatment have been limited [17]. Unfortunately, there is a lack of knowledge of how exercise regimens should be designed to successfully treat chronic WAD [11]. No evidence is available that supports physiotherapy treatment of chronic WAD [17], although exercises are recommended [22]. There are no studies that compare the effect of physical activity, which is commonly prescribed [18], with other approaches, such as neck-specific exercises or a behavioural intervention performed by a physiotherapist. No studies have investigated the outcomes of treatment in terms of the ability of patients to resume work or the cost-effectiveness of different exercise programmes with or without behavioural therapy. Thus, there is a great need for information about which rehabilitation models are effective and cost-efficient.

The aim of this study is to investigate whether neck-specific exercise with or without a behavioural component (facilitated by a single caregiver per patient) improves functioning compared to prescription of general physical activity for individuals with chronic WAD.

## Methods/Design

### Study population

The study will include 216 patients with WAD that has lasted more than 6 months but less than 3 years. The included patients will be randomised into one of the three treatment arms.

#### Eligibility criteria

The inclusion criteria are: Age 18–63 years; WAD grade 2–3 after a whiplash injury at least six months but not more than three years ago, QTF grade 2 includes neck complaints and musculoskeletal sign(s), grade 3 includes grade 2 plus neurological sign(s); Pain intensity > 20 mm on a 100-mm Visual Analogue Scale (VAS) [23] and/or > 20% on the Neck Disability Index (NDI, 0–100%) [24].

Exclusion criteria are: Known or suspected serious physical pathology, including myelopathy, spinal tumour, spinal infection or ongoing malignancy; Earlier fracture or luxation of the cervical column; Neck trauma with persistent symptoms from previous injury; Surgery on the cervical column; Neck pain that caused a > 1 month absence from work in the year prior to the WAD trauma; Signs of traumatic brain injury at the time of WAD (unconsciousness, retrograde or post-traumatic amnesia, disorientation or confusion); Generalised or more dominant pain elsewhere in the body; Diseases or other injuries that might prevent full participation in the study; Diagnosis of a severe psychiatric disorder; Known drug abuse; Insufficient knowledge of the Swedish language (inability to answer the questionnaires).

### Design

This study is a prospective, randomised, controlled, multi-centre study with a 2-year follow-up. Patients will be recruited by searching electronic medical records in five counties in Sweden. Individuals that sought care in the previous 6 to 36 months due to WAD will receive written information that describes the study and that asks whether they are interested in participating. Interested individuals will be screened via questionnaires and telephone interviews by an experienced physiotherapist to determine eligibility and to provide standardised oral information about the study (with a neutral description of the treatment alternatives). Eligible individuals will be asked to undergo a physical examination to ensure that their symptoms are consistent with WAD grade 2 or 3. After providing informed consent, eligible patients will be included in the study. The estimated time period for patient inclusion into the study is 2 years. Next, the patients will be randomised to receive one of three alternative physiotherapy treatments: (A) neck-specific exercise followed by prescription of physical activity; (B) neck-specific exercise with a behavioural approach followed by prescription of physical activity; or (C) prescription of physical activity alone without neck-specific exercises. Treatment will be performed by physiotherapists in primary care centres or private outpatient clinics. The physiotherapists will receive oral and written information about the treatment programs and will participate in an educational session and practice the different interventions. All treatments will be recorded in a diary and in medical records.

Randomisation will be based on a computer-generated list created by the university statistician. This list will assign patient ID numbers to group A, B or C and will be managed by an independent researcher who is not involved in the study in any way. Data from the randomised individuals will be distributed into sequentially numbered, sealed, opaque envelopes. Each envelope will be sent to the treating physiotherapist (in primary care centres or at private outpatient clinics) who will open the envelope and make an appointment with the identified participant. Due to the nature of the treatment, it will not be possible to blind the physiotherapists or the participants to the treatment.

### Outcome measurements

The measurements (clinical measurements and questionnaires) will be collected before treatment and 3, 6 and 12 months after inclusion. Questionnaires will also be collected at a 24-month follow-up. Clinical (neck-related) measurements will be performed in a standardised manner by a well-trained independent investigator who is blinded to the randomisation procedure and who is not involved in the interventions. Independent investigators will also collect the questionnaires. The questionnaires will ask about the patient’s background (including age, gender, social status, education, smoking, pain duration, previous treatment, information about the whiplash trauma and other medical conditions), and about disease-specific information and generic data. The main treatment outcome is neck-specific disability as measured with the NDI [24].

#### Clinical measurements

Clinical measurements includes: Neurological assessment: sensibility, motor function, reflexes, Spurling’s test, neuro-dynamic tests; Active range of motion of the neck in three planes [25] and cervical kinaesthesia (the ability to reproduce the neutral head position from 30° cervical rotation with the eyes closed) [26] as measured with a plastic helmet known as a “cervical range of motion device” [27]; Anterior and posterior neck muscle endurance in seconds in a supine and prone position [28]; Isometric hand grip strength as measured with the Jamar Hand Dynamometer [29]; Static and dynamic clinical balance: static clinical balance as assessed with the Sharpened Romberg test, with eyes closed and the non-dominant foot in front of the dominant foot [30]; dynamic clinical balance as assessed by the patient walking in a figure eight [31].

#### Questionnaires

Primary outcome measure is Neck-specific function: measured with the NDI [24].

Secondery outcome measures contained questionnaires about: Neck pain intensity/ bothersomeness; Pain intensity in the head and arm; Dizziness and unsteadiness: measured with a Visual Analogue Scale (VAS) (0–100 mm) [23]; Domain-specific and general disability related to chronic pain measured with the Pain Disability Index [32]; Dizziness: measured with the UCLA Dizziness Questionnaire [33]; Frequency of symptoms, including neck pain, arm pain, headache, dizziness, visual disturbances, tinnitus, difficulty swallowing and problems concentrating: measured with a 5-grade scale; Pain catastrophising: measured with the Pain Catastrophising Scale [34]; Ability to perform important activities, self-rated by the patient: measured with the Patient-Specific Functional Scale and recorded by the physiotherapist [35]; Confidence in the ability to perform different activities: measured with the Self-Efficacy Scale [36]; Confidence in the ability to perform physical training: measured with the Exercise Self-Efficacy Scale [37]; Physical activity: estimated with the International Physical Activity Questionnaire [38]; Operating fear: measured with the Tampa Scale of Kinesiophobia, short version [39]; Depression and anxiety: measured with the Hospital Anxiety and Depression Scale [40]; Health-related quality of life: measured with the EuroQol-five dimension questionnaire [40], EuroQol thermometer (0–100) [41] and SF-36 [42]; Work conditions, including type of work, work ability and physical demands at work: measured with the Work Ability Index [43]; work-related stress: measured with the Effort Reward Imbalance at work [44]; work satisfaction: measured with various specific questions; The number of sick leave days and extent and disability pension data (collected from the Swedish Social Insurance Agency), the number of sick leave days is also answered on the questionnaire, health care consumption measured with questions about type of caregiver and number of visits.

Questionnaire to determine fulfilment and satisfaction after treatment (to be filled in only after the treatment is completed) are: Treatment success regarding the difference in function after treatment (on a 6-grade scale) and the importance of the difference (0–100-mm VAS scale); Fulfilment of treatment expectations (on a 3-point scale); Satisfaction with the information and care provided measured with the Patient Enablement Instrument (PEI) [45] and an open question.

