#### Group C. Prescription of physical activity alone

Each participant will have one or two appointments to complete a physical examination and a short motivational interview at the physiotherapy clinic. The interview will include determining the patient’s willingness and motivation to adopt new exercise routines and provide information about the benefits of physical activity. The participant will receive a printed copy of individualised, accessible, physical activity instructions that do not include neck-specific exercise. The aim of these activities is to increase the general level of physical activity (i.e. to improve fitness and to elicit the release of endorphins). The activity can be performed in a selected location outside the healthcare environment, such as in the home or at an athletic facility. The participant will be allowed to phone the physiotherapist for further advice regarding their physical activities if needed.

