## Discussion

This is a prospective randomized, controlled, multi-centre trial with blinded assessors who are not involved in the treatment. In order to provide treatment in the participants’ home towns, several physiotherapists will be involved in the treatments. This is a disadvantage in that it will result in decreased control of treatment performance; however, all physiotherapists will undergo the same basic training for the study and will be carefully instructed by the project leaders. Both participants and physiotherapists will keep treatment diaries. This is also an advantage in that it will be possible to generalize the approach to primary health care conditions. Treatments will be individually tailored.

The Swedish Council on Technology Assessment in Health Care has stated that there is a scientific gap in knowledge in terms of the effects of exercise in adults with chronic pain [46]. NHS Evidence from the UK Database of Uncertainties about the Effects of Treatments (DUETs) has also identified both the effects of exercises for mechanical neck disorders (including WAD) [47] and the effects of conservative treatment for whiplash [48] to be important gaps in scientific knowledge. This study will help fill these gaps. The outcome of the study is expected to help improve clinical decision-making for WAD patients. The results will be directly applicable in clinical settings to improve the treatment of patients with chronic WAD.

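### The Patient-Specific Functional Scale is assigned to the physiotherapist, on the natural reading the unblinded treating therapist, which conflicts with the article's statements that independent, blinded assessors measure outcomes

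*Protocol article*

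**What the plan says.** The *Questionnaires* section of the protocol article names the Neck Disability Index as primary outcome and opens its list of secondary outcomes with "Secondery outcome measures contained questionnaires about". One item in that list reads: "Ability to perform important activities, self-rated by the patient: measured with the Patient-Specific Functional Scale and recorded by the physiotherapist". No other instrument in the section is assigned to a physiotherapist.

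Three other places describe who measures outcomes:

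- Abstract, *Methods/Design*: "An independent, blinded investigator will perform the measurements at baseline and 3, 6, 12 and 24 months after inclusion".
- *Outcome measurements*: "Independent investigators will also collect the questionnaires". The preceding sentence says that the clinical measurements are made by an independent investigator who is blinded and has no part in the interventions.
- *Discussion*: the study is a "multi-centre trial with blinded assessors who are not involved in the treatment".

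On the therapists, *Design* says that the treating physiotherapist opens the allocation envelope and that "it will not be possible to blind the physiotherapists or the participants to the treatment". Groups A and B attend the physiotherapy clinic twice weekly, and treatment lasts 3 months. In group C, "Each participant will have one or two appointments to complete a physical examination and a short motivational interview", with telephone advice available if the participant wants it.

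**The concern.** The scale measures whether patients can do the activities that matter to them, in a trial that asks whether neck-specific exercise, with or without a behavioural approach, improves functioning compared with prescribed physical activity. If the *Questionnaires* sentence is followed as written, this one outcome leaves the independent assessment that the rest of the article promises. The person recording it would know the arm and, in groups A and B, would have delivered the treatment. In group B that person would also have helped the patient set activity goals, which is close in content to what the scale measures.

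Two things are at stake. A patient who answers through the treating therapist may answer differently from one who answers an outsider. And the recorder's access to patients differs between the arms while treatment runs, and is not planned in any arm afterwards.

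**Working it through.** The point rests on setting the sections of the article side by side. The only arithmetic is a count of contacts, and no sample-size or power figure bears on it.

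**1. Does the independent-collection rule cover this scale?** *Outcome measurements* defines the measurements as clinical measurements and questionnaires. The scale is listed under *Questionnaires*, so "Independent investigators will also collect the questionnaires" applies to it. The abstract's statement also reaches the questionnaires: it includes 24 months, and *Outcome measurements* adds only questionnaires at that time. No section exempts the scale.

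**2. Who is the physiotherapist?** The descriptions of groups A, B and C use the term for the person who gives the treatment. *Design* has the treating physiotherapist open the envelope. It also mentions an experienced physiotherapist who screens candidates by questionnaire and telephone, but gives that person no follow-up role. The people who assess outcomes are called independent investigators and are never called physiotherapists. The treating therapist is therefore the natural reading, although the sentence does not say so.

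**3. Does that person know the allocation?** Yes, from opening the envelope and from delivering the treatment. *Design* states that blinding of therapists is not possible.

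**4. How much planned contact does the therapist have in each arm?** Inputs: twice weekly (groups A and B), one or two appointments (group C), 3 months of treatment taken as 12 to 13 weeks.

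- Groups A and B: 2 × 12 = 24 to 2 × 13 = 26 sessions each.
- Group C: 1 to 2 appointments, plus optional calls.

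**5. Set this against the measurement times.**

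| Time | Planned therapist contact in A and B | Planned therapist contact in C | Independent collection |
|---|---|---|---|
| During the 3 months of treatment | about 24–26 sessions | 1–2 appointments, timing not given | before treatment |
| 3 months | end of treatment; printed prescription given | none stated | yes |
| 6 months | none stated | none stated | yes |
| 12 months | none stated | none stated | yes |
| 24 months | none stated | none stated | yes (questionnaires) |

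An imbalance between arms in the recorder's access can therefore arise at 3 months. At the three later times the arms are alike, and the difficulty is that no route from the named recorder to the patient is planned in any of them. The independent collection route covers every time point in every arm.

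**The case against.** The strongest reply has four parts.

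*The wording can be reconciled.* The patient gives the rating, a physiotherapist may write it down, and an independent investigator may then collect the form. The sentence does not say treating physiotherapist, although *Design* uses that phrase when it wants to be specific, and the profession of the independent investigators is never given. In *Outcome measurements*, blinding is attached to the clinical measurements, and the questionnaire collectors are called only independent. This stands as far as it goes: the reading is natural, not proven. It does not remove the conflict. The abstract and the *Discussion* speak of blinded assessors without limiting this to clinical measurements, and if a different physiotherapist was meant, the sentence needs correcting to say so.

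*Unequal capture is an inference.* A reader might conclude that the scale would be almost fully recorded in groups A and B, recorded by nobody in group C, and so be useless for comparing A and B with C. The article does not support that. It does not say when the scale is recorded or when the group C appointments fall, it sets one measurement schedule for all participants, and it gives no completeness figure. A count of treatment contacts does not show how often an outcome form is filled in. This part of the objection stands in full.

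*Changing the recorder does not blind the patient.* Participants know their treatment, and every self-reported outcome, the primary one included, shares that limitation. This also stands. Independent recording removes the therapist's influence and the dependence on therapist contact, and nothing more.

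*Who hands out a form is operational detail that a condensed article may leave to the full protocol.* That would answer a silence. Here the article states a recorder, and the statement disagrees with its own general rule.

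**Conclusion.** The concern holds in limited form. As written, the *Questionnaires* section gives one secondary outcome to a recorder who, on the natural reading, is unblinded and delivers the treatment. This conflicts with the abstract, *Outcome measurements* and the *Discussion*.

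The consequence is a risk, not a demonstrated bias. With about 24 to 26 planned sessions in each of groups A and B against 1 to 2 in group C, therapist influence is possible, and so is unequal capture at 3 months. At 6, 12 and 24 months the problem is the same in all arms: the named recorder has no planned contact.

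A reader might infer that any bias must favour A and B. Therapist influence could plausibly act that way, but the direction of an effect from missing data is not determined, and the article gives nothing from which to size either.

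The conclusion assumes that the physiotherapist means the treating therapist and that 3 months is 12 to 13 weeks. The primary outcome and the sample size are untouched. It should still be corrected, because the conflict is plain and the correction is cheap.

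**What to change.** Change the *Questionnaires* sentence so that the Patient-Specific Functional Scale is still rated by the patient but is administered in the same way in all three arms by the independent investigator: at the existing assessments at baseline, 3, 6 and 12 months, and with the 24-month questionnaires. Add that any copy kept by the treating therapist is not used in the outcome analysis.

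If a physiotherapist other than the treating one was meant, the sentence should say so, and should state that this person is independent of treatment, is blinded, and sees all arms on the same schedule.

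The cost is one revised sentence and one form added to assessments that already take place. It needs no further visits or staff.
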